### Sample Size

A management protocol based on EFW and Doppler assessment has shown a prevalence of adverse perinatal outcomes of 26%, meaning that there is a prevalence of 74% of pregnancies with no complications [25]. The estimated rate of pregnancies with no complications in the intervention group has been set at 74%, with a lower limit of 65.5% (a maximum achievable difference of 8.5%). Based on these considerations and an estimated dropout rate of 3%, the sample size needed for a noninferiority design with a power of 80% and a significance level of 5% is 1030 participants, that is, 515 in each group. Noninferiority will be demonstrated if the lower limit of the 95% CI of the difference between incidences of pregnancies without neonatal acidosis is less than –8.5%. If the dropout rate is greater than 3%, the number of participants will be increased so as to achieve 1000 participants with complete data for the primary outcome.

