**Methods:**

This is a multicenter, open-label, randomized controlled trial conducted in 20 hospitals across Spain. A total of 1030 singleton pregnancies with an estimated fetal weight ≤10th percentile at 36+0 to 37+6 weeks+days will be recruited and randomly allocated to either the control or the intervention group. In the control group, standard Doppler-based management will be used. In the intervention group, cases with a soluble fms-like tyrosine kinase to placental growth factor ratio ≥38 will be classified as having fetal growth restriction; otherwise, they will be classified as being small for gestational age. In both arms, the fetal growth restriction group will be delivered at ≥37 weeks and the small for gestational age group at ≥40 weeks. We will assess differences between the groups by calculating the relative risk, the absolute difference between incidences, and their 95% CIs.

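### The stated 1030 women for 80% power do not match the trial's own risk-difference rule, which needs about 864; 1000 evaluable women give about 86.5% power, so the error is conservative

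*Protocol article*

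**What the plan says.** All the inputs are in the protocol article, section Sample Size.

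- **Control rate.** An earlier study of Doppler-based management had 26% adverse outcomes, "meaning that there is a prevalence of 74% of pregnancies with no complications".
- **Intervention rate.** Also 74%, so the assumed true difference is zero.
- **Margin.** The lowest acceptable rate is 65.5%, which is 8.5 points below 74%.
- **Error rates and size.** The section states that "the sample size needed for a noninferiority design with a power of 80% and a significance level of 5% is 1030 participants", or 515 per group. Expected dropout is 3%.
- **Evaluable target.** If dropout exceeds 3%, recruitment continues until 1000 women have complete primary-outcome data.
- **Decision rule.** "Noninferiority will be demonstrated if the lower limit of the 95% CI" for the difference between incidences is on the right side of –8.5%.

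The abstract repeats the total: "A total of 1030 singleton pregnancies". The Statistical Analysis section plans incidence differences and relative risks with 95% confidence intervals. No odds ratio appears anywhere in the article, and the Sample Size section names no formula, software or scale for the calculation.

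**The concern.** In a noninferiority trial, a reader judges the claim from the margin, its scale, the error level and the power together. Here the margin and the decision rule are both stated as a difference in proportions, so the sample size should follow from a risk-difference calculation. It does not.

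Two things are at stake. First, the stated power is not the power of the test that will be run. Second, if the trial was sized on another scale, the article leaves open what the criterion was meant to be. An 8.5-point difference and an odds ratio of about 1.5 agree only when the control rate is 74%. For illustration, suppose the control rate were 80%. The odds are then 0.80/0.20 = 4, and 4/1.499 = 2.668 corresponds to 2.668/3.668 = 72.7%. That is a margin of 7.3 points, not 8.5.

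**Working it through.** **Inputs** (Sample Size section): p = 0.74 in both arms, lower limit 0.655, margin 0.085, power 80% (z = 0.842), dropout 3%. Allocation is 1:1 (Randomization, Masking, and Data Collection section). The lower limit of a two-sided 95% interval corresponds to one-sided 2.5% (z = 1.960). The rule is read as success when that limit lies above –8.5 points, for the composite outcome from which the 74% comes. No adjustment is made for the planned interim look; the section lists dropout as its only allowance.

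**Step 1: trying to reproduce 1030.** Totals include dropout as n/0.97, rounded up per arm, at 80% power and two-sided 5% (one-sided 2.5%).

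| Formula | Per arm | Total with dropout |
|---|---|---|
| Risk difference, variance at 74%/74% | 419 | 864 |
| Risk difference, Farrington-Manning | 419 | 864 |
| Risk difference, continuity-corrected | 442 | 912 |
| Risk difference, variance at 74%/65.5% | 455 | 940 |
| Arcsine | 457 | 944 |
| Superiority, 74% v 65.5% | 458 | 946 |
| Superiority, continuity-corrected | 481 | 992 |
| Log risk ratio, success | 371 | 766 |
| Log risk ratio, adverse outcome | 559 | 1154 |
| **Log odds ratio** | **498** | **1028** |

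Only the last is within 3% of 1030. In detail:

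- OR = (0.74/0.26)/(0.655/0.345) = 1.499, so ln OR = 0.4049.
- n = [2/(0.74 × 0.26)] × (1.960 + 0.842)² / 0.4049² = 497.7, so 498 per arm and 996 evaluable.
- With dropout: 996/0.97 = 1027, or 1028 when rounded up per arm.
- Rounding 996 up to the article's target of 1000 and adding 3% gives exactly 1030.
- Power on this scale with 500 per arm is 80.2%.

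**Step 2: size for the stated rule.**

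n = (1.960 + 0.842)² × 2 × 0.74 × 0.26 / 0.085² = 418.03, so 419 per arm, 838 evaluable, and 838/0.97 = 864 recruited.

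1030/864 = 1.19, so the stated total is about 19% larger.

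**Step 3: power of the stated size under the stated rule.**

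- Standard error with 500 per arm: √(2 × 0.74 × 0.26 / 500) = 0.02774.
- Power = Φ(0.085/0.02774 – 1.960) = Φ(1.104) = 86.5%. A simulation of 400,000 trials also gives 86.5%.
- With all 515 per arm evaluable, power is 87.5%.

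**Step 4: one-sided 5%.** If the 5% were one-sided, the risk-difference calculation would give 330 per arm, 682 with dropout, which is further from 1030. The odds-ratio formula would give 812. The stated total therefore fits the two-sided reading better on both scales.

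**The case against.** The strongest reply is that 1030 is not an arithmetic error. A standard odds-ratio noninferiority formula, fed the article's own figures, gives 996 evaluable women and about 1028 in all at 80% power. The unusual limit of 65.5% is almost exactly an odds ratio of 1.5 from 74%. This stands. A reader might infer that 1030 cannot be derived from the stated inputs, or that 80% is wrong on any basis; neither can be maintained. But the explanation locates the discrepancy without removing it. The margin and the rule are both stated as differences, and for that test 80% is not the power.

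A second reply is that an article condenses a fuller protocol, which may name the formula. Leaving out the formula is indeed no fault in itself. The point rests on figures that the article does print and that disagree with each other.

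A reader might also see a contradiction between a 5% significance level and a 95% interval. There is none. A two-sided 5% level and a two-sided 95% interval are the same convention, equal to one-sided 2.5% at the lower limit. The sidedness is simply not written out.

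Finally, a reader might argue that 1000 women could support a margin of about 7.8 points at 80% power (2.802 × 0.02774 = 0.078), so that 8.5 points is looser than the sample requires. That does not follow. A margin is set on clinical grounds and does not change with the sample size, and power above 80% is not a defect. Deriving a tighter margin from surplus power, in a trial already recruiting, is not warranted.

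**Conclusion.** The point holds in a limited form. For the risk-difference rule in the Sample Size section, 80% power needs 838 evaluable women (864 recruited), not 1000 (1030 recruited). With 1000 evaluable women the power is about 86.5%.

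The likely cause is that the size was calculated on the odds-ratio scale and the decision rule written on the difference scale. That is an inference from the close match at 1028; the article does not say so.

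The discrepancy is conservative. The trial has more power than stated, and the type I error is set by the interval and the margin, neither of which depends on the sample size. Nothing here calls for a smaller trial or a different margin.

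The figures assume 74% in both arms, a fixed-sample normal approximation, and the decision rule read in its evident sense. The printed sentence has problems of its own: it puts the limit below –8.5% and names only neonatal acidosis. Those are separate matters.

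**What to change.** Keep the target of 1000 evaluable women and the 8.5-point margin. In the Sample Size section:

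- state that the test is at two-sided 5%, equivalent to one-sided 2.5% at the lower limit of the 95% confidence interval;
- give the power as about 86% for an 8.5-point risk difference with 500 evaluable women per arm and 74% in both;
- name the formula and scale that produced 1030 and, if it was the odds ratio, say that the criterion for noninferiority is nevertheless the risk difference.

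This is a text correction. It changes neither recruitment, conduct nor the planned analysis. The only work is for the trial statistician to look up the original calculation.

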### Randomization, Masking, and Data Collection

Participants will be randomly assigned to the intervention or control group in a 1:1 ratio using variable-size block randomization. The randomization sequence will be centralized and generated by the web-based system Sealed Envelope (Sealed Envelope Ltd) and will be concealed to investigators. Owing to the nature of the intervention, it will not be possible to conceal the study group to the participants, investigators, or outcome assessors.

A RedCap (Research Electronic Data Capture; Vanderbilt University) electronic database has been specifically designed for this study [64]. The electronic database has a randomization module that will allow allocation of participants to the study groups. Data will be entered prospectively during the study. Access to this database will be restricted to the investigators involved in each participating site.

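### The noninferiority rule has its inequality reversed: as written it is met when a loss beyond the 8.5-point margin has not been excluded

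*Protocol article*

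**What the plan says.** Everything that bears on the decision rule is in the Sample Size section of the protocol article.

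- **Scale and control rate.** The design works with a favourable outcome: "there is a prevalence of 74% of pregnancies with no complications" under management by estimated fetal weight and Doppler.
- **Expected intervention rate.** "The estimated rate of pregnancies with no complications in the intervention group has been set at 74"%, so the planned true difference is zero.
- **Margin.** The intervention rate is given "with a lower limit of 65.5% (a maximum achievable difference of 8.5"%), so a loss of up to 8.5 points is tolerated.
- **Decision rule.** The condition for claiming noninferiority reads: "lower limit of the 95% CI of the difference between incidences of pregnancies without neonatal acidosis is less than –8.5" (in percent).

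The Abstract, the Primary Objective and the Discussion repeat the noninferiority aim without a threshold. The Statistical Analysis section promises differences in incidence and relative risks with 95% CIs, and a type I error level, but no noninferiority criterion. No other place in the article states the rule in the other direction.

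**The concern.** On a favourable scale, a lower limit below –8.5 points means that the data are still compatible with a loss larger than the one the trial is prepared to accept. That is a failure to show noninferiority, yet the article makes it the condition for success. A lower limit above –8.5 points, which is what a successful trial would produce, does not meet the stated condition.

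The sentence is the only threshold given for the primary question, in an open-label trial with an interim analysis at 50% recruitment. If it stays uncorrected, the team must either follow a rule that reverses the conclusion or depart from the published criterion once results are known.

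**Working it through.** **Inputs**

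- Complication-free rate in control: 74% (Sample Size).
- Expected complication-free rate in intervention: 74% (Sample Size).
- Lowest acceptable intervention rate: 65.5% (Sample Size).
- Evaluable participants: 1000, that is 500 per arm (Sample Size; 1:1 allocation under Randomization, Masking, and Data Collection).
- Interval: 95% CI for the difference in incidences (Sample Size). I take it as two-sided, Wald type, with unpooled standard error.

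**Step 1: the plan's own figures.** The margin reproduces: 74 – 65.5 = 8.5 points. The dropout step reproduces: 1000/0.97 ≈ 1031, against the stated 1030. The sample size itself does not follow from the stated inputs. The usual formula at one-sided 2.5% and 80% power, n = 2 × 0.74 × 0.26 × (1.960 + 0.842)² / 0.085², gives 419 per arm, or 864 in total after 3% dropout. That is a separate matter and does not affect the direction of the rule.

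**Step 2: the direction.** Let D = intervention minus control in the proportion free of complications. The hypothesis to be rejected is D ≤ –8.5 points. It is rejected when the lower confidence limit L satisfies L > –8.5. The article requires L < –8.5. The two conditions are complements apart from a tie, so they disagree in any dataset and at any sample size.

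**Step 3: what the written rule does when the arms look equal.** SE = √(2 × 0.74 × 0.26 / 500) = 0.02774, and the half-width is 1.96 × 2.774 = 5.44 points. An observed difference of zero gives L = –5.4 points, which does not meet the written rule. The rule is met only when the observed difference is below about –8.5 + 5.44 = –3.1 points.

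**Step 4: probability of declaring noninferiority.** For a true difference d:

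- SE(d) = √{[0.74 × 0.26 + (0.74 + d)(0.26 – d)] / 500}
- P(L < –0.085) = Φ{(–0.085 + 1.96 × SE – d) / SE}

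At d = 0 this is Φ{(–0.085 + 0.0544) / 0.02774} = Φ(–1.10) = 0.135. At d = –0.085 it is Φ(1.96) = 0.975.

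| True difference (points) | SE (points) | As written, L < –8.5 | Correct direction, L > –8.5 |
|---|---|---|---|
| +4 | 2.70 | 0.4% | 99.6% |
| 0 | 2.77 | 13.5% | 86.5% |
| –5 | 2.85 | 76.8% | 23.2% |
| –8.5 | 2.89 | 97.5% | 2.5% |
| –12 | 2.93 | 99.9% | 0.08% |

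With the inequality corrected, the rule behaves as a noninferiority test should: 2.5% error at the margin and 86.5% power at equality. With 515 per arm the power is 87.5%.

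**Step 5: does the other subtraction order rescue the sentence?** The article does not write the order out, but the 65.5% floor and the negative threshold point to intervention minus control. Under control minus intervention, the correct criterion would be an upper limit below +8.5 points. A lower limit below –8.5 would then require the intervention to look more than about 3.1 points better, which is not a noninferiority criterion either.

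**The case against.** - **The intent is plain.** The 65.5% floor and the stated objective show what was meant, and a statistician is unlikely to apply the sentence literally. This stands. The 97.5% is a property of the rule as printed, not a forecast of a false claim. It does not make the sentence right: a prespecified criterion exists so that nobody has to infer it after seeing data.
- **The probabilities are for the wrong endpoint.** The sentence names pregnancies without neonatal acidosis, whereas 74% is the rate free of the composite. The Introduction reports 46 acidosis cases in a cohort where 134 cases were 26.3%. That implies about 510 pregnancies and about 91% free of acidosis. On that endpoint at 500 per arm, the written rule would declare an equal approach noninferior about 0.3% of the time instead of 13.5%, and one 5 points worse about 59% instead of 76.8%. At 8.5 points worse it stays at 97.5%. So the size depends on the endpoint, but the reversal does not.
- **The rule does not always favour a worse approach.** Correct. At 74%, an approach truly 2 points worse would meet the written rule only about 36% of the time, and a truly equal one still meets it 13.5% of the time. The exact statement is that the rule is met when a deficit beyond the margin has not been excluded.
- **The full protocol and SAP are not shown.** They may already state the rule correctly. That affects where the correction has to be made, not whether the article's sentence is wrong.

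**Conclusion.** The concern holds. The article's only success criterion for its primary objective is reversed, and neither the order of subtraction nor any other section puts it right. The reversal follows from the favourable scale and the negative margin alone; it does not depend on sample size or confidence level.

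The size rests on 500 evaluable participants per arm, 74% free of the composite in control, and a normal-approximation 95% interval. On that basis the written rule turns a 2.5% chance of accepting an approach 8.5 points worse into 97.5%, and an 86.5% chance of accepting an equal one into 13.5%. It is best described as a drafting error, but one that must be corrected before comparative results are seen.

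**What to change.** Replace the sentence in the Sample Size section with:

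> Noninferiority will be demonstrated if the lower limit of the two-sided 95% CI for the difference (intervention minus control) in the proportion of pregnancies free of the primary outcome is greater than –8.5 percentage points.

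This makes three changes, and the correction should name each of them:

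1. The inequality is turned round.
2. The subtraction order is stated.
3. The endpoint becomes freedom from the composite primary outcome in place of freedom from acidosis alone. The Primary Outcome section defines the composite, and the 74% and 65.5% that fix the margin refer to it. Record this as a separate item so that it does not pass as part of a sign correction.

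Publish a dated correction to the article. Check the approved protocol and any SAP for the same sentence, and amend them if they carry it. Do this before any comparative analysis, including the interim. The cost is one sentence in each document concerned, with no additional participants or data.

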### Management of SGA: Feto-Maternal Doppler

In recent years, and after the publication of DIGITAT, several studies have evaluated the role of feto-maternal circulation assessment by Doppler ultrasound in small fetuses [25-28]. These studies have shown that Doppler assessment allows identifying the subset of small fetuses at a higher risk of adverse perinatal outcomes (ie, those with FGR). Historically, umbilical artery (UA) pulsatility index (PI) assessed with Doppler has been considered the standard parameter to identify FGR. However, a large proportion of small fetuses with normal UA PI (ie, <95th percentile) have poorer perinatal outcomes than normally growing fetuses [21,29,30]. Thus, UA PI alone cannot be used to discriminate SGA from FGR fetuses [1,29]. Further studies showed that other Doppler parameters might have a greater predictive ability for adverse outcomes in late-onset SGA and FGR: cerebroplacental ratio (CPR), middle cerebral artery (MCA) PI, and uterine artery (UtA) PI [1,26,31,32]. According to these studies, abnormal CPR (ie, <5th percentile), MCA PI (ie, <5th percentile), or UtA PI (ie, >95th percentile) may be able to identify small fetuses at a higher risk of adverse outcomes (ie, FGR). A study including these criteria showed that small fetuses with abnormal Doppler parameters accounted for 60% of all small fetuses, indicating that more than half of fetuses with an EFW below the 10th percentile would be classified as FGR and that according to our current protocol, early-term induction of labor would therefore be recommended [25]. In the earlier study, induction of labor was recommended at 37 weeks of gestation in FGR fetuses (small fetuses with an EFW below the 3rd percentile or with an EFW below the 10th percentile accompanied by the presence of any abnormal Doppler parameter), while for other pregnancies with an EFW below the 10th percentile (ie, SGA fetuses) induction of labor was recommended at 40 weeks. Following that protocol, 134 cases (26.3%) had an adverse outcome, including, nonexclusively, 46 cases of neonatal acidosis and 106 cases of emergency cesarean delivery due to nonreassuring cardiotocography (CTG). Neonatal acidosis in that study was defined as a UA pH below 7.15 and a base excess greater than –12 mEq/L.

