### Objectives

#### Primary Objective

To determine whether the classification of small fetuses as FGR or SGA based on AFs is not inferior to the standard clinical approach (based on EFW and Doppler percentiles) for the identification of fetuses at a higher risk of adverse perinatal outcomes (neonatal acidosis and cesarean section due to nonreassuring CTG).

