### Outcomes

#### Primary Outcome

The primary outcome is the prevalence of cesarean delivery due to nonreassuring fetal status or the prevalence of neonatal acidosis. Neonatal acidosis will be defined as a UA pH <7.15 and a base excess greater than –12 mEq/L.

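### The noninferiority rule is written on neonatal acidosis alone, while the primary outcome, the 74% planning rate and the 8.5-point margin refer to the composite

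*Protocol article*

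**What the plan says.** The Primary Outcome section has two components: "The primary outcome is the prevalence of cesarean delivery due to nonreassuring fetal status or the prevalence of neonatal acidosis". The Primary Objective names the same pair, "adverse perinatal outcomes (neonatal acidosis and cesarean section due to nonreassuring CTG"), and the Discussion repeats it.

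The Sample Size section starts from a "prevalence of adverse perinatal outcomes of 26%, meaning that there is a prevalence of 74% of pregnancies with no complications". The intervention rate "has been set at 74%, with a lower limit of 65.5" percent, described as "a maximum achievable difference of 8.5" percent. All of these figures refer to freedom from complications.

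The decision sentence in the same paragraph then changes the endpoint. Noninferiority is to be judged on the confidence interval for the "difference between incidences of pregnancies without neonatal acidosis". Cesarean for nonreassuring status is no longer part of it.

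The Statistical Analysis section promises incidence differences and relative risks with 95% confidence intervals for primary and secondary outcomes. It gives no margin and no other success criterion.

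**The concern.** The article states one success criterion, and that criterion names a different endpoint from the one the trial was designed around. An analyst cannot follow both the Primary Outcome section and the decision sentence.

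The difference matters because acidosis is the rarer component. A fixed 8.5-point margin is a much larger relative allowance on a rare event than on a common one, so the test becomes easy to pass. A rise in cesareans for nonreassuring status without acidosis would not enter the verdict at all. The article also says that participants, investigators and outcome assessors cannot be masked. In an open-label trial, two available readings of the success criterion leave room to choose between them after results are known.

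**Working it through.** **Inputs**
- Sample Size: 26% adverse and 74% without complications in control; 74% expected under intervention; lower limit 65.5%; margin 8.5 points; 80% power; 5% significance; 3% dropout; 1030 randomized (515 per arm); target of 1000 with complete data, so about 500 per arm.
- Management of SGA: Feto-Maternal Doppler: 134 adverse outcomes (26.3%) in the source study, including, with overlap possible, "46 cases of neonatal acidosis and 106 cases of emergency cesarean delivery due to nonreassuring cardiotocography (CTG").
- Assumption: the inequality runs in the noninferiority direction (lower limit above –8.5 points), with a Wald 95% interval (one-sided 2.5%).

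**The plan's own figure.** For 74% against 74%, n per arm = 2 × 0.74 × 0.26 × (1.96 + 0.84)² / 0.085² = 419. That is 838 in total, or 864 after 3% dropout. At one-sided 5% it is 330 per arm, or 681 in total after dropout. The stated 1030 was not reproduced; the closest variant tried, a continuity-corrected comparison of 74% with 65.5%, gives 992. The point made here does not depend on this figure.

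**Acidosis rate implied by the source study**
- Denominator: 134 / 0.263 = 509.5.
- Acidosis: 46 / 509.5 = 9.0%. Cesarean: 106 / 509.5 = 20.8%.
- 46 + 106 = 152, which exceeds 134 by 18, so at least 18 cases had both.
- If the 134 contain only these two events, 134 – 46 = 88 of them (66%) are cesareans without acidosis, which the written rule would not count.

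**What the margin leaves open**
- Composite: (26 + 8.5) / 26 = 34.5 / 26 = 1.33.
- Acidosis alone: (9.0 + 8.5) / 9.0 = 17.5 / 9.0 = 1.94.
- Assumed range for control acidosis: at 7%, 15.5 / 7 = 2.21; at 11%, 19.5 / 11 = 1.77.

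**Chance of passing at 500 per arm**, as Φ((0.085 – true increase) / SE – 1.96):
- Composite, equal rates: SE = √(2 × 0.74 × 0.26 / 500) = 0.0277; Φ(3.06 – 1.96) = 86.5%.
- Acidosis, equal rates: SE = √(2 × 0.0903 × 0.9097 / 500) = 0.0181; Φ(4.69 – 1.96) = 99.7%. For 80% power this endpoint would need only 179 per arm.
- Acidosis, 9% to 12%: SE = √((0.09 × 0.91 + 0.12 × 0.88) / 500) = 0.0194; Φ(0.055 / 0.0194 – 1.96) = about 81%.
- Composite 8.5 points worse purely through cesareans without acidosis: the acidosis-only rule still passes about 99.7% of the time. A rule on the composite passes about 2.5%, because the truth then sits at the margin.

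**Highest observed rate that passes.** With 9.0% observed in control and 500 per arm, the largest passing intervention rate is 67 / 500 = 13.4%, a ratio of 13.4 / 9.0 = 1.49.

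**The case against.** The strongest reply is that one phrase slipped. The rest of the Sample Size paragraph speaks of freedom from complications, its next sentence counts participants with complete data for the primary outcome, and the Statistical Analysis section promises an interval for that outcome. A slip is the likeliest explanation. It does not settle the matter, because the slip sits in the only decision rule given and nothing elsewhere overrides it.

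Three stronger readings are tempting, and the documents do not support them.
- *The rule lets acidosis double.* The 17.5% is a true rate that the margin fails to exclude. A true rate there would pass only about 2.5% of the time, and the highest observed rate that passes is about 1.5-fold.
- *A rise in cesareans would go unseen.* It would appear in the primary-outcome estimate. Only the formal verdict, taken literally, would miss it.
- *The pass rates describe the sentence as printed.* The printed sentence asks for the lower limit to fall below –8.5%, which reverses a noninferiority test. Read that way, equal acidosis rates would pass about 0.3% of the time. The rates above assume the intended direction.

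Two cautions also stand. The 9.0% is back-calculated, since the article gives no denominator, and the component list for the source study may not be complete. That the margin was set on exactly these two components is therefore a strong inference from several sections and is not stated outright.

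**Conclusion.** Wrong as written. The endpoint in the decision sentence contradicts the primary outcome and the basis on which the trial was sized, and no section reconciles them. If the sentence were followed literally as to endpoint, the margin's relative allowance would go from 1.33 to about 1.94, and the test would become close to automatic under equal acidosis rates. The mismatch itself rests on the text alone. Its size rests on the derived acidosis rate, 500 evaluable per arm, a Wald interval and the intended direction of the inequality. Across an assumed 7% to 11% control rate the conclusion keeps its direction. Because the sentence determines the trial's verdict, it must be corrected before the analysis.

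**What to change.** In the Sample Size section, replace the decision sentence with one that:
- defines the tested quantity as the difference (intervention minus control) in the proportion of pregnancies with neither cesarean delivery for nonreassuring fetal status nor neonatal acidosis;
- declares noninferiority if the lower 95% confidence limit of that difference lies above –8.5 percentage points. Changing the endpoint alone would leave the reversed inequality in place.

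Report acidosis and cesarean for nonreassuring status separately as components. If a formal noninferiority claim on acidosis is wanted, it needs its own justified margin.

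The cost is a wording correction, with no new data and no change to the sample size. Only the protocol article is at hand, so any separate analysis plan should be checked for the same rule.
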